### Interim analyses {21b}

An interim analysis for safety to evaluate the prespecified stopping rules will be done at 30% and 60% of recruitment by an independent statistician, masked to the treatment allocation. The prespecified clinical and safety stopping rules will be in-hospital mortality rate of more than 40%, a rate of severe intraventricular hemorrhage of more than 30%, and a pneumothorax rate of more than 10%, considering overall occurrences. The data and safety monitoring board will have unmasked access to all data and will discuss the interim analysis results with the steering committee in a joint meeting. The steering committee will then determine the trial’s continuation and report to the central ethics committee.

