#### Criteria for discontinuing or modifying allocated interventions {11b}

On the consent form, participants are informed that they can withdraw from the study at any time without losing any rights to treatment, either current or future. Clinical data will be destroyed only if the right to be forgotten will be requested according to GDPR [ref: https://gdpr-info.eu/art-17-gdpr/]. In this case, the record ID and the allocation arm will be traced, and the reason for withdrawal will be recorded in the eCRF. The trial may be stopped if during the trial or after interim analysis, unwanted effects have occurred, new information becomes available and the experimentation is no longer in the best interests of this population, the agreed rules for participation in the trial are not followed, and the trial is interrupted by the component authorities or by the promoter.

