### Sample size {14}

In order to assess the superiority of the IN-REC-SUR-E with respect to the LISA technique, we hypothesized that employing the IN-REC-SUR-E technique for surfactant administration in extremely preterm infants could lead to an increased survival rate without BPD at 36 weeks of postmenstrual age compared to the LISA approach, raising it from 65 to 80%. Our estimation of a 15% difference is grounded in data from the German Neonatal Network (GNN) regarding the LISA approach, findings from the recently published OPTIMIST trial [27], and updated information on the IN-REC-SUR-E technique from select Italian centers, which continued its use post the conclusion of the INRECSURE study. To achieve 90% statistical power at a 0.05 significance level, we determined that 181 newborns must be enrolled in each group. Factoring in a 5% risk of including patients who do not meet the inclusion criteria after randomization, a total of 382 patients will be randomly assigned. Twins will be randomized separately.

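### The numerical safety stopping rules are set on overall occurrences with no between-arm criterion, so severe harm confined to one arm need not trigger them, and the mortality limit is nearly inert under the trial's own assumptions

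*Protocol article*

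**What the plan says.** All references are to the protocol article.

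- **Interim analyses {21b}, timing.** The safety analysis "will be done at 30% and 60% of recruitment by an independent statistician, masked to the treatment allocation".
- **Interim analyses {21b}, limits.** "The prespecified clinical and safety stopping rules will be in-hospital mortality rate of more than 40" percent, "a rate of severe intraventricular hemorrhage of more than 30" percent, "and a pneumothorax rate of more than 10%, considering overall occurrences". These are the only numerical safety criteria in the document.
- **Interim analyses {21b}, access.** "The data and safety monitoring board will have unmasked access to all data". The board discusses the results with the steering committee, which decides on continuation.
- **Criteria for discontinuing or modifying allocated interventions {11b}.** "The trial may be stopped if during the trial or after interim analysis, unwanted effects have occurred". No number is attached.
- **Sample size {14}.** BPD-free survival is assumed to rise with IN-REC-SUR-E, "raising it from 65 to 80" percent. Death or BPD is therefore assumed to be 35% under LISA and 20% under IN-REC-SUR-E.

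**The concern.** The two arms differ in procedure: intubation with a high-frequency oscillatory recruitment maneuver in one, catheter instillation during CPAP in the other. Harm from a technique would appear in one arm. A rule on the combined rate averages that excess with the other arm, so it measures how sick the whole cohort is rather than whether one technique is worse.

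The mortality limit raises a second question. Death is one component of the primary composite, yet the limit for death alone is higher than the planned rate of the whole composite in either arm. If so, that rule could hardly fire in the trial as designed. At stake is whether the looks at 30% and 60% of recruitment have any prespecified means of picking up technique-specific harm in extremely preterm infants.

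**Working it through.** **1. Design rates reproduced.** Two proportions, two-sided alpha 0.05, power 90%, unpooled variance:

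n = (1.960 + 1.282)² × (0.65×0.35 + 0.80×0.20) / 0.15² = 180.96, so 181 per arm. Then 362/0.95 = 381.05, rounded up to 382.

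Both match the protocol, which confirms 35% and 20% death or BPD as the design rates (average 27.5%).

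**2. Interim sizes.** 0.30×382 = 114.6, about 115 (57 + 58). 0.60×382 = 229.2, about 229 (114 + 115).

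**3. Events needed to exceed each overall limit.**

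| Event | Limit | n = 115 | n = 229 |
|---|---|---|---|
| Mortality | 40% | 47 | 92 |
| Severe IVH | 30% | 35 | 69 |
| Pneumothorax | 10% | 12 | 23 |

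**4. Dilution.** At 1:1 the overall rate is about (pA + pB)/2, so one arm must exceed 2 × limit − the other arm's rate. For mortality that is 70%, 65% or 60% when the other arm is at 10%, 15% or 20%. For IVH it is 55%, 50% or 45% at 5%, 10% or 15%. For pneumothorax it is 18%, 17% or 15% at 2%, 3% or 5%.

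**5. Probability that the overall rule fires.** This is the exact distribution of the sum of two binomials, with the higher rate in the larger arm. The protocol gives no baseline rates for these events, so all the rates below are assumptions.

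| Event | Arm rates | n = 115 | n = 229 |
|---|---|---|---|
| Mortality | 10% v 40% | <0.01% | <0.01% |
| Mortality | 15% v 45% | 0.6% | 0.04% |
| Mortality | 15% v 60% | 25% | 20% |
| Severe IVH | 10% v 40% | 10% | 4% |
| Pneumothorax | 4% v 15% | 42% | 43% |
| Pneumothorax | 5% v 20% | 80% | 90% |

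With exactly equal arms (57 + 57, 114 + 114) the figures move slightly, for example 0.8% and 0.03% for mortality 15% v 45%. For mortality and IVH the chance falls at the second look, because the overall rate settles below the limit.

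**6. Mortality limit against the design.** 40% exceeds 35% (LISA) by 5 points and the 27.5% average by 12.5 points. Take the extreme case in which every assumed primary event is a death (35% v 20%). The rule then fires with probability about 0.1% at n = 115 and 0.002% at n = 229. This result uses only the protocol's own rates.

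**7. Applying the same limits to each arm.** This would catch mortality of 45% in an arm of 57 with probability 80%, and in an arm of 114 with 86%. The cost is in false alarms. At n = 115 with pneumothorax truly 8% in both arms, the chance that an arm exceeds 10% is 0.304 (57 infants) and 0.318 (58 infants). At least one does so with probability 1 − 0.696×0.682 = 53%, against 21% for the overall rule. With 5% in both arms the figures are 13% and 1.3%.

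**8. A between-arm comparison instead.** A pooled-variance z test at one-sided p<0.01, summed over the exact binomials, detects mortality of 15% v 45% with probability about 0.90 and 0.997 at the two looks. With equal true rates between 5% and 15% it raises a false alarm about 1% of the time or less, per event, look and direction.

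**The case against.** Several points on the other side are sound.

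- **A reader might infer that one-arm harm cannot trigger these rules.** The documents do not support that. A large enough excess does, and pneumothorax, the event most directly tied to the recruitment maneuver, fires 80% and 90% of the time at 5% v 20%. The rules are insensitive rather than blind, chiefly for mortality and IVH.
- **Other safeguards exist.** The DSMB sees unmasked data and monitors adverse events. Data go to the principal investigator and advisory board under coded group labels. The same three events must be reported within 24 hours, each serious event has a causality review, and the general clause permits stopping for unwanted effects. An imbalance would be visible to people able to act. This stands and lowers the severity. None of it supplies a criterion, however.
- **The basis of the rates is a reading.** Overall occurrences might mean all occurrences whatever their timing or attribution, and a masked statistician could also work with coded arms. Both arms combined remains the likeliest meaning.
- **An absolute alarm is meant to sit above plan.** A reader might infer that the mortality limit contradicts the sample size section. It does not: it counts in-hospital deaths, the composite is assessed at 36 weeks, and the limit could matter if the design assumptions failed badly. The remark is one of calibration.
- **The event rates are assumed**, and 15% v 45% is an extreme split. This is so for every scenario except the one built on 35% v 20%.

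**Conclusion.** The point holds in this form: the stated rules are a poor detector of technique-specific harm, clearly so for mortality and severe IVH and much less so for pneumothorax. The mortality rule is nearly inert if the sample size assumptions are right.

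The conclusion rests on reading the limits as both arms combined, on 1:1 allocation at about 115 and 229 infants, and, for sizes, on assumed event rates. The dilution itself and the comparison of 40% with 35% and 20% need no assumed rate. Because an unmasked board has discretion to act, this is something that should be fixed. It does not show that the trial lacks safety oversight.

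**What to change.** In Interim analyses {21b}, and in the DSMB charter if there is one:

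1. Say explicitly that the three limits apply to both arms combined, and keep them as an absolute alarm.
2. Add that the three events are tabulated by arm at each look, with a prespecified, non-binding between-arm comparison in each direction (for example one-sided p<0.01). The masked statistician can run it on coded arms.
3. State that the by-arm results go to the DSMB only, and adjust the sentence on the joint meeting with the steering committee to match.
4. Ask the sponsor and DSMB to reconcile the mortality limit with the sample size assumptions, or to record why it sits above them. No value is proposed here.

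Do not simply apply the existing limits to each arm, for the false-alarm reason shown in the working.

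The cost is some wording and one by-arm table. The false-alarm chance is about 1% or lower per event, look and direction. With 3 events, 2 looks and 2 directions, a crude upper bound is 3×2×2×1% = 12% for any alarm in the trial, which is tolerable because the comparison only prompts the board's review.

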### Methods for additional analyses (e.g., subgroup analyses) {20b}

Subgroup analyses will be conducted to explore specific factors such as gestational age influencing the outcomes, providing a more nuanced understanding of the intervention’s effects within distinct subpopulations.

### Methods in analysis to handle protocol non-adherence and any statistical methods to handle missing data {20c}

Considering the variables collected and the planned control in the data collection procedure, we do not anticipate a high percentage of missing data. Each reported information will be systematically checked for consistency, completeness, data processing, and monitoring (refer to paragraph **{**18b**}**). For these reasons, no imputation will be provided for missing data.

### Plans to give access to the full protocol, participant-level data, and statistical code {31c}

The datasets analyzed during this trial are available from the corresponding author upon reasonable request.

### Duration of study

In this study, 382 infants will be recruited. The trial will terminate when the last recruited infant discharged from the hospital will be evaluated for neurodevelopmental outcome and respiratory function at 24 months of follow-up. The planned duration for randomization is 3 years.

### Oversight and monitoring

#### Composition of the coordinating center and trial steering committee {5d}

A joint Trial Steering Committee (TSC) and Data and Safety Monitoring Board (DSMB) will provide supervision for the trial, providing advice to the chief and co-investigators on all aspects of the trial conduct and affording protection for patients by ensuring the trial is conducted according to the Guidelines for Good Clinical Practice in Clinical Trials. The chief investigator and advisory board will chair the TSC. A trial manager, a statistician, and other investigators will form the DSMB. The trial manager and other investigators will check randomly the accuracy and consistency of the data entered from the participating centers. The data will be reported to the PI and advisory board as “group A” and “group B.” An independent statistician, blinded to the treatment allocation, will perform the interim analysis. The statistician will report to the DSMB. The DSMB will have unblinded access to all data and will discuss the results of the interim analysis with the Steering Committee in a joint meeting. The Steering Committee will decide on the continuation of the trial and will report to the central Ethics Committee.

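### The DSMB is drawn from trial staff and investigators, and its joint meeting with the Steering Committee and the A/B reporting could expose trial leadership to comparative results

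*Protocol article*

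**What the plan says.** All references are to the protocol article. The data monitoring item {21a} gives no text of its own and points back to section {5d}, so {5d} is the operative description.

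- **Structure.** "A joint Trial Steering Committee (TSC) and Data and Safety Monitoring Board (DSMB) will provide supervision for the trial".
- **Membership.** "A trial manager, a statistician, and other investigators will form the DSMB". None of these people is described as independent of the trial.
- **Operational role.** "The trial manager and other investigators will check randomly the accuracy and consistency of the data entered from the participating centers".
- **Steering Committee.** "The chief investigator and advisory board will chair the TSC".
- **Labelled reporting.** "The data will be reported to the PI and advisory board as" two labelled groups, A and B.
- **Access and sharing.** Of the board, {5d} specifies: "unblinded access to all data and will discuss the results of the interim analysis with the Steering Committee in a joint meeting". Interim analyses {21b} repeats that the board is unmasked and that it "will discuss the interim analysis results with the steering committee in a joint meeting". Both sections leave the decision on continuation to the Steering Committee.

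The only party called independent is the masked statistician who runs the interim analysis. That analysis is for safety, at 30% and 60% of recruitment. Its limits are absolute rates of in-hospital death, severe intraventricular hemorrhage and pneumothorax, counted over both arms together. The blinding section {17a} makes allocation known to parents, local site research staff and medical teams after randomization.

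**The concern.** A monitoring board is meant to let someone look at results by arm without those who run the trial learning them. Here the board with full access consists of trial staff and investigators, it sits in a joint structure with the Steering Committee, and it discusses interim results with that committee in one meeting. Masking the interim statistician protects little when the report goes to an unblinded board of this kind.

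The design has few other defences against such knowledge. Treatment is open label. Escalation from CPAP to bilevel support or NIPPV is left to the neonatologist on duty, and all usual care is allowed. An infant still on CPAP at 36 weeks' postmenstrual age is classed as having BPD with no room-air challenge. Knowing which arm is ahead could influence whom a site enrols, how an infant is supported and when CPAP is withdrawn, and so the primary outcome.

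**Working it through.** The point rests on no design figure; it is mainly a comparison of statements. The arithmetic only shows whether by-arm data at the interim looks could be informative.

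**1. What each party can see**
- DSMB: everything, unblinded ({5d}, {21b}). Its members are a trial manager, a statistician and other investigators.
- Steering Committee: whatever is raised in the joint discussion of the interim results. No closed session or limit on content is stated.
- PI and advisory board: data under two group labels ({5d}). They also chair the Steering Committee.
- Sites: the arm of each of their own infants ({17a}). Anyone who holds A/B summaries and knows the allocation of some infants can probably work out the labels, and so can anyone who meets the unblinded board.

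**2. What the formal rules need**

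The three stopping limits in {21b} are pooled rates. Pooled counts are enough to apply them, so the rules themselves do not require the Steering Committee, PI or advisory board to see data by arm.

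**3. The stated sample size**

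Inputs from Sample size {14}: 65% against 80%, power 90%, significance level 0.05 (taken as two-sided, which the text does not state), 1:1 allocation. With unpooled variance:

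n = (1.960 + 1.282)² × (0.65×0.35 + 0.80×0.20) / 0.15² = 180.96, so 181 per group.

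The total is 362/0.95 = 381.05, so 382. Both stated figures reproduce.

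**4. How informative by-arm data could be**

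The looks fall at 0.30 × 382 = 114.6 (about 115) and 0.60 × 382 = 229.2 (about 229) infants. If the design difference is true and the primary outcome is complete for all of them, the expected z is 0.15 / √[(0.2275 + 0.16)/n per arm]:
- first look, 57.5 per arm: 0.15/0.0821 = 1.83;
- second look, 114.5 per arm: 0.15/0.0582 = 2.58.

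These are optimistic, because the outcome is known only 8 to 12 weeks after birth (36 weeks minus 27+6 or 24+0). Assuming even accrual over the planned 3 years, 382/156 ≈ 2.45 infants a week, about 20 to 29 infants would be pending at each look.
- First look: 86 to 95 infants with outcome, expected z 1.58 to 1.66.
- Second look: 200 to 209 infants with outcome, expected z 2.41 to 2.46.

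By-arm primary data at these times could therefore show a visible trend. The protocol does not say that such data are tabulated at the interim looks. These figures do not measure bias.

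**The case against.** The strongest reply is that the planned interim is narrow: safety only, run by a masked statistician, with pooled limits. On that reading the joint meeting may discuss nothing more than three overall rates. This stands as a description of the formal rules, and several stronger readings fail because of it.

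- A reader might infer that by-arm interim results are certain to reach the chief investigator. The text does not say so. The A/B sentence does not mention the interim analysis and follows the sentence on data checks; the PI and advisory board get coded labels, not named arms.
- A reader might infer that DSMB members treat trial infants. The text says only other investigators; it neither states nor excludes this.
- A reader might infer inflated type I error from repeated efficacy looks. The protocol contains no interim test of the primary outcome and no efficacy boundary, so an error rate for such testing would describe a procedure that is not planned.
- A reader might fault the Steering Committee for deciding on continuation. That is not a defect in itself; what matters is what it has seen beforehand.

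It is also fair that discretion over respiratory support exists in any open-label trial, and that infants on high-flow therapy or on oxygen below 0.30 undergo a standardized reduction test. Only the additional influence of knowing the running comparison belongs to this point. Voting rules and report formats usually sit in a charter that an article need not reproduce.

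What remains is what the article states: a board drawn from trial staff and investigators, unblinded to everything, meeting jointly with the chief investigator's committee, alongside A/B reporting. No section shown supplies a firewall, and a charter that did so would conflict with an unrestricted joint discussion.

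**Conclusion.** The concern holds in a limited form. As written, the arrangement could expose trial leadership and investigators to comparative results, through unblinded access, the joint meeting and A/B reporting rather than through the stopping rules. Whether exposure occurs depends on what is shown at the meeting and on how easily the labels are decoded, neither of which the document settles. The resulting operational bias cannot be computed from the document. The case for change is that the safeguard costs little, the endpoint is partly discretionary, and knowledge once shared cannot be withdrawn.

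**What to change.** Revise {5d} and {21b}, and align the DSMB charter, so that:

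1. By-arm interim data go only to the DSMB, in a closed report.
2. The DSMB gives the Steering Committee only a recommendation to continue, modify or stop, with no joint review of by-arm results. The Steering Committee may still take the decision.
3. The PI and advisory board receive pooled data only, in place of group A and group B. This is enough to apply the pooled stopping limits.
4. Where membership can be reassigned, DSMB members do not enrol or treat trial infants, assess outcomes, manage the trial or sit on the Steering Committee.

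The cost is redrafting, some reassignment of members, and less insight for the Steering Committee while the trial runs. Sample size, assessments and treatment are unchanged. Because the article reports that recruitment is under way, the change should be in place before the next interim look.

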#### Composition of the data monitoring committee, its role, and reporting structure {21a}

Refer to above {5d}.

#### Adverse event reporting and harms {22}

Adverse events, device deficiency, and incidents, as identified by the following definitions, will be recorded and reported to the Manufacturer and the National Competent Authority as per applicable law (for EU Centers Regulation 2017/745 and Centers in Italy Circular of the Ministry of Health Application of the EU Regulation 2017/745 of the European Parliament and of the Council, of 5 April 2017, in the field of clinical investigations relating to medical devices).

Site investigators will report any adverse event to the coordinating center. In case of a serious event involving a medical device, serious incident, a report (for centers located in Italy from Dispovigilance—https://www.salute.gov.it/DispoVigilancePortaleRapportoOperatoreWeb/) will be issued and sent to the Competent Authority, the manufacturer, and the coordinating center, as per national applicable law. Device deficiency will be reported by the investigators to the coordinating center and to the manufacturer, as per applicable law.

Adverse events, device deficiency, and incidents will be identified by the following definitions:*Incident* means any malfunction or deterioration in the characteristics or performance of a device made available on the market, including use error due to ergonomic features, as well as any inadequacy in the information supplied by the manufacturer and any undesirable side effect; “serious incident” means any incident that directly or indirectly led, might have led, or might lead to any of the following: (a) the death of a patient, user, or other persons; (b) the temporary or permanent serious deterioration of a patient’s, user’s, or other persons’ state of health; and (c) a serious public health threat.*Device deficiency* means any inadequacy in the identity, quality, durability, reliability, safety, or performance of an investigational device, including malfunction, use errors, or inadequacy in information supplied by the manufacturer.*Adverse event* means any untoward medical occurrence, unintended disease or injury, or any untoward clinical signs, including an abnormal laboratory finding, in subjects, users, or other persons, in the context of a clinical investigation, whether or not related to the investigational device.*Serious adverse event (SAE)* means any adverse event temporally related to the procedure that led to any of the following situations during hospitalization: (a) death and (b) serious deterioration in the health of the subject that resulted in any of the following: (i) life-threatening illness or injury, (ii) permanent impairment of a body structure or a body function, (iii) hospitalization or prolongation of patient hospitalization, (iv) medical or surgical intervention to prevent life-threatening illness or injury or permanent impairment to a body structure or a body function, and (v) chronic disease secondary to adverse events related to the procedure.

Safety end-point measures will include incidence, severity, and causality of reported serious adverse effects, namely changes in the occurrence of the expected common complications of prematurity and clinical laboratory test assessments and the development of unexpected SAEs in this high-risk population. All SAEs will be graded according to Common Terminology Criteria for Adverse Events (CTCAE) version 5.0. All SAEs and serious incidence (SI) will be followed until satisfactory resolution or until the investigator responsible for the care of the participant deems the event to be chronic or the patient to be stable. Particular attention will be paid to the SAEs (in-hospital mortality, serious intraventricular hemorrhage, and pneumothorax) considered stopping rules. They have to be inserted by local investigators in the eCRF and reported to the PI and advisory board as soon as possible, no later than 24 h after their occurrence.

